## Abstract

**Introduction:**

Infant upper respiratory microbiota are derived partly from the maternal respiratory tract, and certain microbiota are associated with altered risk of infections and respiratory disease. *Neisseria lactamica* is a common pharyngeal commensal in young children and is associated with reduced carriage and invasive disease by *Neisseria meningitidis*. Nasal inoculation with *N. lactamica* safely and reproducibly reduces *N. meningitidis* colonisation in healthy adults. We propose nasal inoculation of pregnant women with *N. lactamica*, to establish if neonatal pharyngeal colonisation occurs after birth, and to characterise microbiome evolution in mother–infant pairs over 1 month post partum.

**Methods and analysis:**

20 healthy pregnant women will receive nasal inoculation with *N. lactamica* (wild type strain Y92-1009) at 36–38 weeks gestation. Upper respiratory samples, as well as optional breastmilk, umbilical cord blood and infant venous blood samples, will be collected from mother–infant pairs over 1 month post partum. We will assess safety, *N. lactamica* colonisation (by targeted PCR) and longitudinal microevolution (by whole genome sequencing), and microbiome evolution (by 16S rRNA gene sequencing).

**Ethics and dissemination:**

This study has been approved by the London Central Research Ethics Committee (21/PR/0373). Findings will be published in peer-reviewed open-access journals as soon as possible.

**Trial registration number:**

NCT04784845.

Strengths and limitations of this studyThe *Neisseria lactamica* controlled human infection model is well-characterised, with safety, dosing, immunological and genomic data from over 400 adult participants to date.This is the first prospective study of horizontal respiratory commensal acquisition in neonates following controlled human infection in pregnancy.Longitudinal sampling of multiple respiratory niches in mother–infant pairs allows for microbiome characterisation over time.The small sample size may be insufficient to demonstrate a significant association between *N. lactamica* inoculation and microbiome changes.No causal association between *N. lactamica* inoculation and observed microbiome changes can be concluded in the absence of a control group.

## Introduction

### Upper respiratory pathobionts and infant disease

Upper respiratory tract (URT) pathobionts are common colonising bacteria capable of causing disease in immunocompetent individuals (eg, *Neisseria meningitidis, Streptococcus pneumoniae, Haemophilus influenzae*). Although harmless in many hosts, these remain a leading cause of global childhood death and disease, especially in the first year of life: globally, 492 000 and 89 000 infants die each year due to respiratory tract infection (RTI) and meningitis, respectively.^1^ While many infant infections are vaccine-preventable, global access to and acceptance of vaccines remains incomplete, such that 1.5 million vaccine-preventable childhood deaths occur each year.^2^ Furthermore, existing vaccines do not protect against all important childhood respiratory pathogens (such as respiratory syncytial virus and some serotypes of *S. pneumoniae*), and vaccinations are not routinely given in the first 2 months post partum, when risk of invasive infection is highest. Rising global antimicrobial resistance compounds these challenges, with 214 000 neonates dying of resistant infections each year.^3^

Recent research has highlighted the relationship between URT pathobionts, childhood disease and the evolving infant microbiome (the site-specific total microbial community).^4^ Taxonomic profiling (eg, by bacterial 16S rRNA gene sequencing) demonstrates distinct URT microbiota during acute RTI, and that URT microbiome perturbation is associated with RTI severity and recurrence, childhood chronic wheeze and early allergic sensitisation.^5–8^

Infant RTIs are often preceded by micro changes, including increased relative abundance of URT pathobionts and loss of topography (blurring of distinction between microbiomes at adjacent anatomical sites),^9^ suggesting a possible causal role in developing infection. However, as up to 93% of infants are colonised with at least one URT pathobiont at any time,^10^ pathobiont colonisation alone is not necessarily associated with infection: rather, the presence of pathobionts may indicate a state of dysbiosis (microbial dysregulation), in which disease-causing bacteria and viruses can cause infection in a previously resilient ecological niche.

Longitudinal cohort microbiome studies suggest that infant URT flora are acquired at least in part from their mothers: there is greater overlap between a neonate’s oral flora and that of its own mother than unrelated mothers, and shared bacterial strains (detected by whole genome sequencing) are more long-lived in an infant’s mouth than non-maternal strains.^11^ Moreover, a subset of maternal oral strains account for a disproportionately large share of their infants’ oral flora.^11^

### Can upper respiratory microbiota be manipulated to prevent infant disease?

In the future, it is possible that simple methods of modifying the infant nasopharyngeal microbiome could provide useful adjunct protection in the early months of life.^12^ Previously, neonatal nasal inoculation with low-virulence *Staphylococcus aureus* strain 502A has been shown to reduce colonisation by high-virulence *S. aureus* strain 80/81 in response to an outbreak,^13^ while pharyngeal inoculation with strain 215 alpha-haemolytic streptococci reduced pharyngeal pathobionts (*Escherichia coli, Klebsiella pneumoniae, S. aureus*) in neonatal intensive care inpatients.^14^ Furthermore, a variety of probiotics (living microorganisms administered to confer a health benefit) have been trialled in children and adults, with some reporting a reduction in upper RTI incidence and duration.^15^ However, high quality efficacy and microbiome data is lacking, with significant inter-study variation in the bacterial strain (usually lactobacilli, streptococci and bifidobacteria), preparation (usually capsules or dairy supplement), dose and regimen. That being said, there is evidence that many probiotics are safe in pregnancy, neonates and lactating mothers, with some already available over-the-counter to these groups.^16^

### Controlled human infection with *Neisseria lactamica*

Unlike probiotic studies (which often employ proprietary food supplements with uncontrolled concentrations of bacteria), controlled human infection offers a robust model for studying the impact of a defined bacterial inoculum on a human host. Our research group has previously developed a safe and reliable controlled human infection model using nasal inoculation with 10^4^–10^5^ colony-forming units (CFU) *N. lactamica* strain Y92-1009 in healthy adults.^17 18^ In randomised blinded placebo-controlled studies, we have characterised *N. lactamica* colonisation density, duration, cellular and humoral immune responses, and genomic microevolution,^19^ observing colonisation rates of up to 85% and no serious adverse reactions following over 400 inoculations.

*N. lactamica* is a common non-capsulated pharyngeal commensal that does not cause invasive disease in immunocompetent hosts. Colonisation peaks at over 40% in 1–2 year-old children,^20^ before falling to less than 10% in adulthood,^21^ and *N. lactamica* carriage correlates inversely with *N. meningitidis* colonisation.^22^ Indeed, *N. lactamica* controlled human infection in healthy adults reduced naturally-acquired *N. meningitidis* carriage from 18% to 8% (both by displacing existing colonisation and preventing new acquisition), exceeding the typical impact of glycoconjugate ACWY vaccination.^17^ This displacement effect is not specific to a particular serogroup, unlike available glycoconjugate meningococcal vaccines. Furthermore, natural colonisation with *N. lactamica* has been observed to correlate inversely with invasive meningococcal disease.^21^

### Rationale for this study

The aim of this study is to establish if nasal inoculation with *N. lactamica* in pregnancy results in neonatal colonisation after birth, and to characterise the impact on the developing neonatal URT microbiome. If successful, this will provide a novel model for inducing and studying person-to-person commensal acquisition in neonates (unlike traditional controlled human infection models, which capture inoculation-induced colonisation). Looking ahead, this may provide a new strategy for reducing *N. meningitidis* colonisation and disease in neonates, and of modifying neonatal microbiome development with a view to improving health outcomes.

## Methods and analysis

### Study overview

In this prospective controlled human infection study, 20 healthy pregnant women will receive nasal inoculation with 10^5^ CFU *N*. *lactamica* (wild type strain Y92-1009) at 36+0 to 37+6 weeks gestation (figure 1). Upper respiratory samples and breastmilk will be collected from mother–infant pairs 1 day, 1 week and 1 month post partum, as well as an umbilical cord blood sample at delivery and an infant venous blood sample at 1 month post partum. Adverse events and relevant clinical data (including mode of delivery, infant feeding and use of antimicrobials) will be recorded. Samples will be analysed by microbiological culture, targeted PCR and sequencing to determine *N. lactamica* Y92-1009 presence, colonisation density and longitudinal microevolution, as well as 16S rRNA gene sequencing to characterise microbiome evolution in mother–neonate pairs.

**Figure 1 F1:**
[figure not shown]
Study overview flowchart. API, analytical profile index; CFU, colony forming units; h, hours; m, months; MALDI, matrix-assisted laser desorption/ionisation; Nlac, *Neisseria lactamica*; w, weeks.

### Study hypothesis, objective and endpoints

We hypothesise that nasal inoculation of pregnant women with 10^5^ CFU *N*. *lactamica* strain Y92-1009 will result in maternal upper respiratory *N. lactamica* colonisation; and that horizontal transmission of upper respiratory *N. lactamica* will occur from experimentally-colonised women to their infants by 4 weeks post partum.

This study aims to investigate this hypothesis, and to characterise the safety, colonisation kinetics and microbiome impact of nasal *N. lactamica* inoculation in pregnancy on mother–neonate pairs (table 1).

**Table 1 T1:** Primary, secondary and safety study endpoints

Primary endpoint Confirmation of neonatal (0–31 days) *Neisseria lactamica* colonisation by selective culture of nasopharyngeal and saliva samples.	Secondary endpoints Confirmation of neonatal *N. lactamica* Y92-1009 colonisation by strain-specific PCR. *N*. *lactamica* colonisation density in inoculated volunteers compared with their infants across study time points and sample niche. Microbiome composition across study time points and sample niche in inoculated volunteers compared with their infants, and in colonised compared with uncolonised infants. *N*. *lactamica* genome sequence for isolates derived from inoculated volunteers compared with their infants across study time points and sample niche.
		Safety endpoints Percentage of inoculated volunteers with adverse reactions or serious adverse events within the study period. Percentage of neonates with serious adverse events within the study period.

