### Statistical analysis

The primary endpoint will be expressed as a proportion N/M, where:

M=Number of mothers colonised with *N. lactamica*.N=Number of neonates (aged 0–31 days) colonised with the same strain of *N. lactamica* as their own mother.‘Colonised’=evidence of *N. lactamica* by culture of upper respiratory swabs (using selective media and confirmation by API or MALDI-TOF) on at least one visit.‘Same strain’=confirmed using Y92-specific *N. lactamica* PCR for inoculated volunteers, or whole genome sequencing for volunteers already naturally carrying *N. lactamica* at screening.

Subgroup analysis will be performed, to compare inoculated mother–infant pairs with naturally colonised mother–infant pairs, and to compare pairs where the mother or infant received antibiotics with pairs not receiving antibiotics.

Specific bioinformatic analysis strategies will depend on the quantity and quality of genomic data produced during the study, and on the rates of *N. lactamica* colonisation observed. Broadly speaking, microbiome bioinformatic pipelines (eg, QIIME2 and R packages) will be used to perform taxonomic classification, calculation of alpha and beta diversity and data visualisation.

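### The primary endpoint is any-strain culture positivity in Table 1 but the mother's own strain in the Statistical analysis section, and the sample-size benchmark fits only the first

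*Protocol article*

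**What the plan says.** Three sections of the protocol article bear on the primary endpoint.

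- **Study hypothesis, objective and endpoints, Table 1.** The primary endpoint is neonatal (0–31 days) *N. lactamica* "colonisation by selective culture of nasopharyngeal and saliva samples". No strain is named and no denominator is given. Neonatal Y92-1009 "colonisation by strain-specific PCR" is the first of the secondary endpoints.
- **Statistical analysis.** "The primary endpoint will be expressed as a proportion N/M". The numerator is "N=Number of neonates (aged 0–31 days) colonised with the same strain of" *N. lactamica* as the infant's own mother. The denominator is "M=Number of mothers colonised with" *N. lactamica*, not restricted to inoculated mothers. Colonised means culture positive on at least one visit. The strain match rests on Y92-specific "PCR for inoculated volunteers", or on "whole genome sequencing for volunteers already naturally carrying" *N. lactamica* at screening.
- **Sample size.** The calculation takes 18 experimentally colonised mothers (90% of 20). It sets a bar of 22% infant colonisation (95% CI 2.3% to 41.7%) against natural infant carriage of 2.3% by 1 month, with no strain specified for that rate.

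**The concern.** The two definitions count different infants. An infant of an inoculated mother who acquires a wild strain, for example from a sibling, meets Table 1's primary endpoint but does not enter N. For inoculated pairs, the analysis section also moves Table 1's first secondary endpoint into the primary one.

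The definitions answer different questions. One concerns carriage of the species in the infant. The other concerns transfer from the mother, which is what the stated hypothesis is about. The sample-size benchmark fits the first question and the analysis section the second.

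The denominators do not line up either. Table 1 has none, the Sample size section uses experimentally colonised mothers only, and M as worded also takes in naturally colonised mothers who stay in the study as a comparison cohort.

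In a trial likely to turn on a handful of events, one infant can matter, and the rule for counting that infant should be settled before results are seen.

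**Working it through.** **Inputs.** Expected colonised mothers 18, natural infant carriage 2.3%, bar 22% (2.3% to 41.7%), 24 or more women screened, and 10% baseline maternal carriage, all from Sample size. That Y92-1009 can be told apart from natural strains comes from the section on the strain-specific PCR.

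**1. The plan's own figure.** A Wald interval with n − 1 in the standard error reproduces it:
0.22 ± 1.96 × √(0.22 × 0.78 / 17) = 0.22 ± 1.96 × 0.1005 = 2.3% to 41.7%.
By the same method, 4/18 (22.2%) has a lower limit of 2.5%, which clears 2.3%. For 3/18 (16.7%) the lower limit is −1.0%, which does not. In whole infants, the bar is 4 of 18.

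**2. Which infants count.**

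| Infant of an inoculated, colonised mother | Table 1 primary | N in Statistical analysis |
|---|---|---|
| Culture positive, Y92-1009 | yes | yes |
| Culture positive, non-maternal strain only | yes | no |
| Culture negative | no | no |

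N is a subset of Table 1's count. The definitions differ only in the middle row.

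**3. Size of the middle row.** At 2.3% background:
- expected background carriers: 18 × 0.023 = 0.41
- chance of at least one: 1 − 0.977^18 = 1 − 0.658 = 34%
- weight of one infant: 1/18 = 5.6 percentage points

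The first two are upper figures for the middle row, because a background carrier who also carries Y92-1009 could count under both definitions.

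**4. Chance that the bar is crossed under one definition only.** Let S be the number of infants with the mother's strain, S ~ Binomial(18, p). Let W be the number with only a wild strain, W ~ Binomial(18 − S, 0.023), acquired independently. The definitions disagree about the bar when S ≤ 3 and S + W ≥ 4:

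P = Σ (s = 0 to 3) P(S = s) × P(W ≥ 4 − s)

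| True transfer rate p | P |
|---|---|
| 5% | 2.5% |
| 10% | 6.6% |
| 15% | 8.5% |
| 20% | 7.7% |
| 25% | 5.5% |
| 30% | 3.3% |

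Most of this comes from S = 3. At p = 15%, P(S = 3) = 0.241 and P(W ≥ 1 among 15) = 0.295, giving 7.1 of the 8.5 percentage points.

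**5. Denominator.** With 24 screened and 10% naturally colonised, 24 × 0.10 = 2.4 mothers could enter M as worded, on top of the 18 in the sample-size calculation, if they stay in the study.

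**6. Benchmark.** The 2.3% has no strain attached. Under the same-strain definition, background in infants of inoculated mothers would be close to zero. This is an assumption, based on the article's statement that the Y92 band pattern has not been seen in natural isolates. Against that endpoint, 2.3% is a conservative comparator rather than a matched one.

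**The case against.** The strongest reply is that the Statistical analysis section simply makes Table 1 computable. It keeps culture as the basis, adds the strain condition, and is the only place where numerator and denominator are fixed. Table 1 is silent on strain rather than saying any strain, and the same-strain reading fits the hypothesis. On this view the analysis section governs and a cross-reference would do.

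Much of that stands: the two texts agree on the assay, and a reader could reasonably infer which governs. It does not remove the problem. Table 1 places strain confirmation in a different tier, and the Sample size section compares with a species-level rate, which fits Table 1 better.

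Two stronger readings are tempting and unsupported:

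- **That there is a 34% chance of a changed conclusion.** The 34% is the chance of at least one background carrier among 18. A changed conclusion also needs the same-strain count to lie just below the bar. Background may also be lower than 2.3% here, since inoculated mothers screened negative and the article says infant flora come partly from the mother. The cliff between 3 and 4 infants depends on the Wald-type bar as well: the exact 95% lower limit for 3/18 is 3.6%, already above 2.3%.
- **That the abstract gives a third definition by mentioning targeted PCR.** It lists what will be assessed and by which methods, and does not mention the primary endpoint.

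It is also fair that this is a single-arm proof-of-concept study with a pragmatic sample size, and that culture and strain-specific results are both listed endpoints.

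**Conclusion.** The point holds as a contradiction on the primary endpoint. An infant carrying only a non-maternal strain counts in Table 1 and not in the Statistical analysis section. The denominator and the 2.3% benchmark are not aligned with a single definition either. Because both definitions are written out, condensation into an article does not explain the difference.

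The size is modest: at most 0.41 affected infants expected among 18, each worth 5.6 percentage points, and a 2.5% to 8.5% chance that the stated bar is met under one definition only. These figures assume 18 colonised mothers, 2.3% background, independence between background acquisition and maternal transfer, true transfer rates of 5% to 30%, and the plan's own bar.

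A reader might infer that the primary analysis cannot be carried out. The documents do not support that, since N/M is computable as written. What is missing is one definition used consistently.

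**What to change.** State one primary endpoint in Table 1, Sample size and Statistical analysis, before outcome data are examined:

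- **Numerator:** culture-confirmed neonatal (0–31 days) *N. lactamica*, identified as Y92-1009 by strain-specific PCR.
- **Denominator:** inoculated mothers who become colonised. Amend M and the strain-matching rule in Statistical analysis to suit.
- **Naturally colonised pairs:** report separately, matched by whole genome sequencing, in the subgroup comparison already planned.
- **Secondary endpoint:** any-strain neonatal culture positivity, in place of the present strain-specific entry.
- **Benchmark:** in Sample size, apply the 2.3% comparison to the any-strain endpoint, or say that it is a conservative benchmark for the strain-specific one.

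The abstract can stay as it is. The cost is a coordinated text edit in three sections. Changing Table 1 alone would leave a new mismatch with M and with the 2.3% comparison. No new sample or assay is needed, because culture, the strain-specific PCR and sequencing are already planned.

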### *N. lactamica* inoculum

Vials of lyophilised (freeze-dried) *N. lactamica* (LyoNlac) will be produced and stored under Good Manufacturing Practice (GMP)-like standards at the University of Southampton. The strain used for lyophilisation (Y92-1009, sequence type 3493, clonal complex 613) originates from the current GMP-compliant pharmaceutical manufacturing facilities at Public Health England (Porton Down, UK). Lyophilised inoculum stocks can be stored at 4°C (unlike frozen stocks requiring storage at −80°C). LyoNlac will be reconstituted in phosphate buffered saline and diluted to a concentration of 10^5^ CFU/mL for inoculation. In our previous work, this dose resulted in *N. lactamica* colonisation in 100% of 10 adults receiving lyophilised inoculum and 85% of 20 adults using frozen inoculum (ie, 90% overall). The inoculum will be administered immediately following reconstitution and serial dilution, and after no more than 30 min delay; recovery of viable bacteria remains over 70% after 30 min incubation in room air (unpublished data).

### Recruitment of study volunteers

All potentially eligible healthy adult volunteers in the second and third trimesters of pregnancy will be identified by research midwives using a clinical database, and will be sent an ethically-approved study advertisement and a Participant Information Sheet. Individuals who express an interest will be invited to attend a screening visit. Participants will be offered reimbursement for their time, travel and inconvenience.

### Study visits and procedures

#### Screening

Interested individuals will be reviewed by the study doctor at a screening visit (34+0 to 36+6 weeks gestation), to discuss the study timeline and procedures (table 2) and assess eligibility (box 1). Eligible individuals who provide informed consent at screening will be considered enrolled. A detailed medical history will be taken, followed by pharyngeal and saliva sampling to assess for *N. lactamica* carriage; enrolled volunteers who are already naturally colonised with *N. lactamica* will not be inoculated. However, they will be invited to remain in the study as an opportunistic comparison cohort, and will complete all postpartum visits and sampling as for the inoculated mother–neonate pairs (table 2).

Box 1Inclusion and exclusion criteriaInclusion criteria (all must apply)Healthy adult aged 18 years or over on the day of enrolment.Singleton pregnancy, 34+0 to 36+6 weeks gestation on the day of enrolment.Documentation of a 20-week ultrasound scan with no life-limiting congenital anomalies, and no maxillofacial, otorhinolaryngological or neuroanatomical anomalies.Able and willing (in the Investigator’s opinion) to comply with all study requirements.Able and willing to give written informed consent to participate in the study.Booked to receive antenatal care at University Hospital Southampton NHS Foundation Trust (including any associated community antenatal care facilities), UK.Exclusion criteria (none must apply)Any confirmed or suspected immunosuppressive or immunocompromised state, including: HIV infection; asplenia; recurrent severe infections; or use of immunosuppressant medication (for more than 14 days within the past 6 months, excluding topical and inhaled steroids).Planned use of immunosuppressant medication in later pregnancy or post partum.Occupational, household or intimate contact with any immunosuppressed persons.Participation within the last 12 weeks in a clinical trial involving receipt of an investigational product, or planned use of an investigational product during the study period.Prior participation at any time in research studies involving inoculation with *N. lactamica*.Use of oral or intravenous antibiotics within 30 days prior to the inoculation visit.Planned use of oral or intravenous antibiotics at any time during the study period (eg, for planned elective caesarean section or group B streptococcus colonisation).Allergy to soya or yeast.Previous stillbirth or neonatal death.Pre-pregnancy diabetes mellitus.Any other finding that may (in the Investigator’s opinion): increase the risk to the volunteer (or their fetus/infant or close contacts) of participating in the study; affect the volunteer’s ability to participate in the study and complete follow-up; or impair interpretation of study data.

**Table 2 T2:** Study visits and activities

Timeline	Screening (visit 1)	Inoculation (visit 2)	Birth (visit 3)	Follow-up (visits 4 and 5)		Optional (visit 6)
	34+0 to 36+6 weeks gestation	36+0 to 37+6 weeks gestation	0–24 hours post partum	7±3 days post partum	28±3 days post partum	15±2 weeks post partum
Participant Information Sheet and consent form	**+**					
Clinical review	+	+	+	+	+	+
*Neisseria lactamica* nasal inoculation		+ (Unless already colonised)				
Nasopharyngeal swabs (mother)	+	+	+	+	+	+
Oropharyngeal swabs (mother)	+	+	+	+	+	+
Saliva swabs (mother)	+	+	+	+	+	+
Nasopharyngeal swabs (infant)			+	+	+	+
Saliva swabs (infant)			+	+	+	+
Umbilical cord blood			Optional			
Infant venous blood (2 mL)					Optional	Optional
Maternal breast milk			Optional	Optional	Optional	Optional
Maternal venous blood (5 mL)						Optional
Oropharyngeal and saliva swabs (under 5 years)						Optional

